## Abstract

**Background:**

Suboptimal uptake of anticoagulation for stroke prevention in atrial fibrillation has persisted for over 20 years, despite high-level evidence demonstrating its effectiveness in reducing the risk of fatal and disabling stroke.

**Methods:**

The STOP STROKE in AF study is a national, cluster randomised controlled trial designed to improve the uptake of anticoagulation in primary care. General practitioners from around Australia enrolling in this ‘distance education’ program are mailed written educational materials, followed by an academic detailing session delivered via telephone by a medical peer, during which participants discuss patient de-identified cases. General practitioners are then randomised to receive written specialist feedback about the patient de-identified cases either before or after completing a three-month posttest audit. Specialist feedback is designed to provide participants with support and confidence to prescribe anticoagulation. The primary outcome is the proportion of patients with atrial fibrillation receiving oral anticoagulation at the time of the posttest audit.

**Discussion:**

The STOP STROKE in AF study aims to evaluate a feasible intervention via distance education to prevent avoidable stroke due to atrial fibrillation. It provides a systematic test of augmenting academic detailing with expert feedback about patient management.

**Trial registration:**

Australian Clinical Trials Registry Registration Number: ACTRN12611000076976.

## Background

Atrial fibrillation (AF) is the most common heart arrhythmia with a prevalence of around 5% in those aged over 65, increasing to 10% in those older than 75 years [1]. AF confers the highest risk for ischaemic stroke of all traditional risk factors, including congestive heart failure, diabetes, and hypertension [2]. In Australia, at least one in four patients admitted to hospital with an ischaemic stroke has AF [3]. Mortality in stroke patients with AF is around twice the rate in those without it; by 12 months, 40% of ischaemic stroke patients with AF will have died [3]. Moreover, survivors of AF-related stroke spend a significantly longer time in hospital [3].

Meta-analyses of randomised controlled trials of antithrombotic medication demonstrate that, in the average AF patient with a 5% chance of an ischaemic stroke each year, oral anticoagulation with adjusted-dose warfarin reduces this annual risk by 67%, in relative terms, to approximately 1.7% [4]. In contrast, antiplatelet medication, such as aspirin, reduces the risk by only 21%, to approximately 4% [4]. Despite over 20 years of evidence supporting lifelong anticoagulation as the treatment of choice for most patients with AF [4-6], 50%–60% of patients do not receive anticoagulants even if they are at high risk of stroke [7,8]. An Australian study of 218 consecutively admitted patients with AF reported that only 20% were using warfarin on admission [9], although inclusion of an unspecified number of newly diagnosed AF cases would have influenced the reported proportion of under use [9]. In a Canadian stroke unit, 90% of admitted ischaemic stroke patients with AF were not receiving anticoagulation or were insufficiently anticoagulated at the time of their stroke [10]. In one Australian stroke unit, 68% of ischaemic stroke patients with known AF before admission either were not anticoagulated or were sub-optimally anticoagulated at the time of their stroke [11]. This persistent evidence–practice gap contributes to the burden of preventable stroke.

Clinicians are often reluctant to prescribe anticoagulation for AF, particularly if patients are elderly or have a heightened risk of falls or other perceived risk of major bleeding [12-19]. However, many patients considered unsuitable for anticoagulation also have an elevated risk of ischaemic stroke, and the risk-benefit trade-off favours anticoagulation in the majority of patients with AF [20-24].

Few studies have evaluated implementation strategies specifically designed to increase the uptake of oral anticoagulation for AF. McAlister *et al.*[25] reported an increase in antithrombotic prescribing at three months in general practice patients receiving a decision aid. The difference was not sustained at 12 months after randomisation. In a nonrandomised study of Australian primary healthcare physicians in one geographical region of Tasmania, guideline dissemination followed by academic-detailing visits significantly increased prescribing rates of adjusted-dose warfarin compared to a control region [26]. Two other studies in the primary healthcare setting addressed several cardiovascular risk factors, without focusing specifically on AF management [27,28]. Ornstein *et al.*[27] tested the effect of computerised guidelines, reminder systems, and audit and feedback on prescribing behaviour in managing several cardiovascular risk factors. Posttest differences between intervention and control groups were not statistically significant. Another trial found that locally adapted guidelines, an educational seminar delivered by local opinion leaders, educational materials, and an offer of an educational outreach visit did not increase primary healthcare physicians’ adherence to prescribing guidelines for patients with a history of transient ischaemic attack (TIA) or AF [28]. The outcome measure in this study did not distinguish between anticoagulant and antiplatelet prescribing.

Other randomised evaluations of implementation strategies have been carried out with stroke survivors to optimise secondary prevention [29-33]. These have included few AF patients (n = 6 to n = 99) [29-33], and of the two studies reporting outcomes for AF patients, neither found statistically significant improvements in anticoagulant prescribing [32,33].

Specialist decisional support for general practitioners (GPs) merits further investigation. A recent evaluation of a shared-care model for stroke survivors involved liaison between GPs and stroke specialists, facilitated via a nurse specialist. The study found significant improvements in the management of secondary stroke risk and, for AF patients, a nonsignificant improvement in anticoagulation prescribing attributable to the intervention [32]. However, the total number of AF patients in this study was small (n = 32). While the multifaceted nature of the study intervention precludes the identification of effective components, it suggests that linking GPs with stroke specialists could enhance clinical decision making. An observational study also reported a significant effect of collaborative involvement between specialists and GPs on appropriate anticoagulation prescribing, providing further support for the hypothesis that specialist input may be effective in improving the management of AF patients [34].

In another study, known as DESPATCH, we are evaluating the effect of expert decisional support to promote the uptake of anticoagulation using feedback from clinical experts in stroke medicine [35]. However, in the DESPATCH study, decisional support is embedded within a multifaceted intervention including written educational materials, three telephone academic-detailing sessions, and a workshop/seminar. We have designed the STOP STROKE in AF study to systematically assess the impact of expert decisional support on the management of AF in a national study.

## Methods

Please see attached file (Additional file 1) for the study flow diagram.

### GP recruitment

We obtained contact details of GPs from a commercially available database [36], which sources information from professional colleges, medical directories, and state medical boards that register all practising clinicians in Australia. After an initial pilot with 100 randomly selected GPs to determine the likely participation rate, we undertook recruitment in two phases, obtaining lists of 3,000 randomly selected GPs from across Australia in 2010 and 2,501 in 2011 (with those selected in 2010 removed from the sampling frame). GPs who were participating in another implementation trial about AF we were carrying out [37] were excluded from the randomly selected samples (n = 10 in 2010 and n = 13 in 2011).

GPs were mailed a brief introductory letter inviting them to complete a registration form, to be returned by fax or an enclosed business reply paid envelope, advising us of their interest in an education program about stroke prevention. During the first (*i.e.*, in 2010) and second phases of recruitment (*i.e.*, in 2011), we carried out two randomised trials of response-aiding strategies, both of which received ethics approval as amendments to the main study protocol. During the first phase, a statistician independent of the research team randomised 2,250 GPs into three equal-sized groups (n = 750 for each group). The first group was mailed the introductory letter and registration form in an institutional 110 mm by 220 mm-sized envelope (DL-sized) with the university logo and address printed in black and white on the top left-hand corner. The second group was mailed the letter and form in the institutional envelope and also received complimentary copies of resources provided free of charge by the National Stroke Foundation (NSF) of Australia. The third group was also mailed the NSF resources with their letter and form but received these via an Australia Post “Express Post” envelope representing “priority mail”. The remaining 740 GPs were not included in this trial and were mailed the introductory letter and registration form at a different time point to those selected to test response-aiding strategies. During the second wave of recruitment, 2,488 GPs were randomly divided to receive the cover letter and registration form printed on pale yellow (n = 1,247) or white paper (n = 1,240). Letters were mailed using the institutional DL-sized envelopes with logo and address printed in black and white. This trial was separately registered (ACTRN12611000259943).

GPs who returned their registration forms were mailed an information sheet and a consent form, advising that consenting GPs would be invited to participate in an educational session delivered by a medically trained peer via telephone, after which they would be randomised to receive specialist feedback about the de-identified patient cases (see description of intervention below). GPs who returned a signed consent form by fax or enclosed reply paid envelope were then mailed educational materials in advance of a telephone educational session to be delivered by medical peers. Only those GPs who complete the telephone educational session, providing pretest data, are considered recruited and eligible for randomisation. During the initial stages of the first recruitment phase (*i.e.*, in 2010), GPs returning their registration form were telephoned in advance of receiving the information sheet and consent form, and those GPs not returning a consent form within a minimum of two weeks were mailed a second copy. However, due to resource constraints, this follow-up protocol was abandoned.

### Academic detailing

Enrolled GPs receive printed education materials (see Additional file 2) prior to being contacted by a medically trained peer who carried out a standardised telephone educational session covering key issues concerning the management of AF (see Additional file 3). Topics include the epidemiology of AF [1-3], risk stratification using the validated tools [37], and information about the benefits and risks of antithrombotic medications used to manage AF, including adjusted-dose warfarin and antiplatelet medication, such as aspirin and/or clopidogrel [38-44]. During 2011, the information was revised to include information about a revised risk stratification scheme [45] and dabigatran [46-48], a newly available fixed-dose anticoagulant that received regulatory approval in Australia for stroke prophylaxis in AF in May 2011.

GPs were advised in advance of the telephone educational session to identify patients with AF who are over the age of 65 and not receiving anticoagulation or for whom anticoagulation management had presented difficulties. GPs enrolled during the first phase of recruitment (*i.e.*, in 2010) were advised to select around three or four patients for discussion with the medical peer, while those recruited during the second phase (*i.e.*, from 2011 onwards) were advised to select a minimum of five patients.

At the conclusion of the telephone educational session, the medically trained peer proceeded through a standardised patient *pro forma*, collecting de-identified information about patient demographics, stroke risk factors, other comorbidities, current antithrombotic medications, and issues relevant to anticoagulation use. Medically trained peers calculated the patient’s CHADS_2_ score with participating GPs, providing general feedback based on evidence-based guideline recommendations, according to patients’ CHADS_2_ scores [24]. The CHADS_2_ score assigns two points for prior stroke or TIA and one point each for the following risk factors: congestive heart failure, history of hypertension, age over 75, and diabetes. Key safety messages about stroke risk in paroxysmal AF, hypertension, and use of antithrombotic treatment in patients with a history of spontaneous intracranial haemorrhage were also communicated. From late 2011, medical peers also communicated a safety alert issued by the peak Australian drug regulatory body, the Therapeutics Goods Administration (TGA), about the risks of using dabigatran, a newly available oral anticoagulant, in the elderly and in patients with renal impairment [49].

### Pretest data collection

Before commencing the academic-detailing session, medical peers noted GPs’ gender and asked participants to report the number of doctors in their practice and whether they were practising full-time or part-time. Medical peers asked GPs whether they had any of the following resources available to assist them in managing AF patients receiving warfarin: a nurse to monitor and recall patients when needed; automated or computerised reminders for noting when patients need to have their International Normalised Ratios INR levels tested; point-of-care INR testing; pathology service anticoagulation management; or hospital clinical anticoagulation management, practice-based register, or utilisation of a formal Australian government program whereby pharmacists visit patients to monitor compliance with medications. A modified version of the Provider Decision Process Assessment Instrument [50] measuring GP levels of decisional conflict regarding warfarin use was administered. GPs were asked to indicate their level of agreement (agree, disagree, neither) to five statements (‘Whether or not to prescribe warfarin is a difficult decision to make’, ‘For most patients it is clear that warfarin is the best treatment’, ‘It is often difficult to decide if the benefits of warfarin outweigh the risks, or vice versa’, ‘Generally, patients fully appreciate the benefits of warfarin’, ‘Generally, patients fully appreciate the risks of warfarin’). Finally, medical peers asked GPs whether they had participated in formal educational activities about AF in the previous 12 months.

The de-identified patient *pro forma* document contributed to the pretest patient-level data for this study. Information on patient age and sex was first elicited. GPs were then asked to clarify whether the patient had paroxysmal or chronic AF (a response of unsure was permitted) and whether the patient had underlying valvular heart disease or nonvalvular AF. Medical peers asked GPs to indicate if the patient had thyrotoxicosis (yes/no/unsure). Relevant medical history ascertaining stroke risk factors to enable calculation of the CHADS_2_ score was elicited. History of myocardial infarction, peripheral artery disease, aortic plaque, coronary artery disease, and high cholesterol/hyperlipidemia was also noted, as was current smoking status.

Relevant comorbidities reflecting actual or perceived contraindications to anticoagulation were also elicited. These included the following: falls history (without and without injury), a history of multiple falls, anaemia, recent or current upper gastrointestinal (GI) bleeding within the last month, history of upper GI bleeding, history of lower GI bleeding, history of GI bleeding (location not specified), a treated cause of GI bleeding, cerebral haemorrhage, hepatic insufficiency/moderate to severe liver disease, impaired kidney function, chronic dialysis, renal implantation, abnormal serum creatinine (>200 ųmol/L), hepatic derangement on biochemical testing, excessive alcohol intake (defined as eight or more units per week), coagulopathy, thrombocytopaenia, dementia or cognitive impairment (with and without supervised care), insertion of coronary artery stent (drug-eluting, bare metal, or stent of unknown type), and nonadherence with medication or management. Comorbidities assessing bleeding risk as described above were derived from a standardised scheme [51]. GP participants could nominate other comorbidities they considered relevant for specialist feedback. The *pro forma* elicited information on current antithrombotic medications; previous use of anticoagulation with adjusted-dose warfarin; and, where relevant, reasons for not using warfarin, for ceasing warfarin, and adverse events whilst receiving warfarin (minor bleeding not requiring hospitalisation, major blood loss requiring hospitalisation, intracranial or intracerebral haemorrhage, including subarachnoid haemorrhage; ischaemic stroke; TIA or amaurosis fugax; sub-therapeutic INR levels; supra-therapeutic INR levels; consistently unstable INR levels). Rate- or rhythm-control medications, non-steroidal anti-inflammatory drugs (NSAIDs) including COX-2 inhibitors, paracetamol, alternative medications, and other over-the-counter medications in current use were also noted. From 2011 onwards, GPs were asked to note, where relevant, adverse events whilst receiving anticoagulants other than warfarin (most likely dabigatran).

### Randomisation

A statistician external to the study group is carrying out randomisation after participants complete academic-detailing sessions. Randomisation is being stratified by the number of cases GPs identify (≤2 or >3). Results of randomisation are communicated to the study coordinator (MG) who assigns GPs to their respective groups. The statistician involved in the analysis of the trial will receive the randomisation schedule directly from the statistician carrying out randomisation. Block randomisation is being used to control for date of entry into the trial. Block size will be disclosed to the study team only during the write-up of results.

### Expert decisional support

Medically trained peers reminded GPs that they will be randomised to receive specialist feedback about patient de-identified cases either prior to or after posttest evaluation. They were advised to consider this component of the intervention as an educational exercise and, therefore, should not have expectations of timely feedback and should seek any urgently required advice through their usual practices. Data from the de-identified *pro forma* documents were mailed to MG, who entered the data and summarised information into a one- to two-page document that was forwarded to experts in either neurology, cardiology and stroke. The experts provided written information that was then mailed to GPs randomised to receive expert decisional support prior to the posttest phase of the study (see Additional file 4 for a hypothetical example). Our model for delivering this aspect of the intervention was informed by an intervention developed by McAlister *et al.*, 2006 [52].

### Waiting list control

GPs randomised to the waiting list control group were mailed a summary of patient de-identified information, identical to the summary received by GPs randomised to the intervention arm. These GPs also received a statement summarising patient ischaemic stroke risk based on the patient’s CHADS_2_ score. Therefore, patient summaries were identical between groups, with the exception of specialist written feedback.

### Posttest data collection

Posttest data collection is scheduled for approximately 12 weeks after GPs have received either the expert decisional feedback or, for those randomised to the waiting list control group, the patient de-identified summary document. GPs receive another copy of the patient de-identified summary sheet (without expert feedback) attached to a brief posttest questionnaire. For each patient, GPs are asked to indicate current antithrombotic treatment from a list of available choices (warfarin, aspirin, clopidogrel, aspirin and clopidogrel, dipyridamole, dipyridamole with aspirin, dabigatran, other antithrombotic for GP to specify, or no antithrombotic) and, if currently receiving warfarin, to report the last six INR test results and corresponding dates of blood collection. In response to a checklist of items, GPs are asked to specify reasons for any given patient not receiving anticoagulation (patient refusal/reluctance, history of traumatic brain haemorrhage, history of spontaneous brain haemorrhage, history of lower GI bleed, history of upper GI bleed, falls history without injury, falls history with injury, history of GI location not specified, age, cognitive impairment, inadequate supervision at home, patient nonadherence with medication, patient nonadherence with monitoring, specialist doesn’t recommend anticoagulation, patient at low risk of stroke, awaiting government subsidisation of fixed-dose anticoagulation with dabigatran, or other reason which GPs are asked to specify).

Whether or not patients are receiving anticoagulation, GPs complete an adapted version of the Provider Decision Process Assessment Instrument [50], consisting of six items assessing GP levels of decisional conflict regarding anticoagulation with adjusted-dose warfarin, with an additional question asking GPs to indicate their level of satisfaction with the current treatment. From 2011 onwards, the posttest evaluation included an additional six questions assessing levels of decisional conflict for a newly available fixed-dose anticoagulant, dabigatran. Posttest data will be entered by personnel blinded to group allocation.

### Primary outcome

The primary outcome is defined as the proportion of patients with AF who, at posttest, are reported by GPs to be receiving anticoagulation.

### Secondary endpoints

#### Appropriate antithrombotic treatment according to stroke risk

In accordance with evidence-based guidelines [38-40], we will use baseline CHADS_2_ scores in those patients aged over 65 years to judge appropriateness of antithrombotic management. Specifically, patients over 65 years of age with a baseline CHADS_2_ score of 0 will be considered to be managed appropriately if receiving aspirin, while those with a baseline CHADS_2_ score of 2 or more will be considered to be receiving appropriate antithrombotic treatment if receiving anticoagulation (either with warfarin or dabigatran). Either anticoagulation or aspirin will be considered appropriate in those with a baseline CHADS_2_ score of 1. The expected few cases of patients younger than 65 years of age will be excluded from this analysis. However, a sensitivity analysis will be carried out applying the CHADS_2_ score to patients younger than 65 years of age, as above, in recognition of inclusion criteria used in recent trials of antithrombotic treatments that included patients younger than 65 where AF was associated with CHADS_2_ stroke risk factors [4-6].

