#### Appropriate antithrombotic treatment according to stroke risk incorporating quality-control criteria

In those patients receiving anticoagulation with warfarin, we will only consider anticoagulation to be appropriate for this outcome if GPs, when reporting the six most recent INR results, report an INR result at least monthly and where at least four of the six test results (or two-thirds of results in cases where fewer than six are reported) are within therapeutic range (*i.e.*, within 2.0–3.0). These criteria for appropriate anticoagulation are based on local guidelines [44] and a consistently achieved standard of ‘time in therapeutic range’ reported in clinical trials [4-6], including one trial of general practice patients with an average age of 81 years [6].

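### The two CHADS2-based appropriateness outcomes ignore valve status, which is recorded at pretest, so a valvular patient at CHADS2 0 fails on anticoagulation and passes on aspirin

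*Protocol article*

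**What the plan says.** All references are to the protocol article.

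- **Case selection** (Academic detailing): GPs are advised to "identify patients with AF who are over the age of 65 and not receiving anticoagulation or for whom anticoagulation management had presented difficulties". Nothing there or elsewhere excludes valve disease.
- **Pretest form** (Pretest data collection): for each case the GP is asked "whether the patient had underlying valvular heart disease or nonvalvular AF". This is recorded before randomisation, because only GPs who have completed the telephone session and given pretest data can be randomised.
- **Score** (Academic detailing): an earlier stroke or TIA counts double; the remaining items carry "one point each for the following risk factors: congestive heart failure, history of hypertension, age over 75, and diabetes".
- **Outcome rule** (Appropriate antithrombotic treatment according to stroke risk): "we will use baseline CHADS_2_ scores in those patients aged over 65 years to judge appropriateness of antithrombotic management". At the lowest score, "patients over 65 years of age with a baseline CHADS_2_ score of 0 will be considered to be managed appropriately if receiving aspirin". Anticoagulation or aspirin is accepted at score 1, and anticoagulation is needed at 2 or more. Patients under 65 are left out, with a sensitivity analysis that brings them back.
- **Quality-control version**: the same rule, with INR conditions added for patients on warfarin.
- **Further refinement of outcome definition**: where aspirin is the reference treatment, other antiplatelets and their combinations also count.

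**The concern.** The article collects valve status on every case and then does not use it in any outcome definition, sensitivity analysis, subgroup analysis or pretest comparison. The two appropriateness outcomes give every patient over 65 a label based on a score that cannot see valve disease. At CHADS2 0 the label depends wholly on whether the patient receives an anticoagulant or an antiplatelet.

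The comparison between arms is where this could matter. The tested component is case-specific written advice from experts in neurology, cardiology and stroke. Control GPs receive the same patient summary with a risk statement based on CHADS2. If an expert gives weight to valve disease and the GP starts an anticoagulant in a patient at score 0, that patient moves from pass to fail. Using the same rule in both arms does not ensure that such cases cancel, because the advice is what differs between the arms.

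**Working it through.** **1. Can the case arise?** Selection requires AF, age over 65, and either no anticoagulation or difficulty with it. The score gives an age point only above 75. A patient aged 68 with valve disease and no heart failure, hypertension, diabetes, stroke or TIA meets the selection advice and scores 0.

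**2. How is that patient scored?** From the outcome rule and its refinement:

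| Baseline CHADS2 | Anticoagulant at posttest | Aspirin or other antiplatelet at posttest |
|---|---|---|
| 0 | not named, so not appropriate | appropriate |
| 1 | appropriate | appropriate |
| 2 or more | appropriate | not named, so not appropriate |

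Valve status appears nowhere in this table. At score 0 the refinement widens the accepted treatments to antiplatelets only, which confirms the first row. Anticoagulation is penalised only at score 0.

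**3. The plan's own sample size.** With 50% against 65%, two-sided 0.05 and 80% power (power and sidedness are my assumptions, as neither is stated), the usual two-proportion formula without continuity correction gives 170 per group, or 340 in total, as stated. Then 340 × 1.06 = 360.4, rounded up to 361; 361 / 0.80 = 451.25, rounded up to 452. The figures reproduce and this point does not alter them. The base for the count below is 361, the number expected after 20% non-return.

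**4. How many patients?** No frequency is given in the documents, so these inputs are assumptions:

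- v, share with valvular disease: 2% to 15%
- c, share of these at CHADS2 0: 5% to 20%
- w, share of those on an anticoagulant at posttest: 50% to 65% (the two rates in the sample size section)

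Valvular, score 0 and anticoagulated, hence scored not appropriate: 361 × v × c × w

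- low: 361 × 0.02 × 0.05 × 0.50 = 0.18 (0.05%)
- high: 361 × 0.15 × 0.20 × 0.65 = 7.04 (1.95%)

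All valvular patients at score 0, on whatever treatment: 361 × v × c

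- low: 361 × 0.02 × 0.05 = 0.36
- high: 361 × 0.15 × 0.20 = 10.83

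**5. Effect on the arm difference.** Suppose anticoagulation in these patients rises by the planned 15 points. Counting that shift as failure instead of success moves the overall difference by 2 × 0.15 × v × c. This is 0.03 percentage points at v × c = 0.001, and 0.9 percentage points at v × c = 0.03.

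**The case against.** The strongest reply is that nothing in the article says valve disease changes the right treatment. The rule rests on cited guidelines that cannot be consulted here. Many other recorded items, such as smoking, cholesterol and peripheral artery disease, also enter no outcome, and the pro forma has a stated use of its own: it is summarised for the experts. This part stands. A reader might infer that the rule marks correct treatment of valvular patients as wrong; the documents do not support that, because they set no treatment for these patients.

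A reader might also extend the point to thyrotoxicosis, which is recorded and equally absent from the score, or to the single INR range of 2.0 to 3.0 in the quality-control outcome. Neither extension holds on the text. No section says that thyrotoxicosis calls for separate handling, or that valvular patients have a different INR target.

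It can further be said that analysis-set detail belongs in an analysis plan that is not shown. That is weaker here. The article itself fixes the rule, its age exclusion, an age sensitivity analysis and a refinement for aspirin intolerance, coronary stenting and acute coronary syndromes. Having gone to that level, it leaves out a baseline field that it collects on every case, although its own Discussion uses the term nonvalvular AF.

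Finally, a patient stable on warfarin at pretest is not the kind of case GPs were asked to select. True, but a patient untreated or on aspirin at pretest who starts an anticoagulant by posttest is, and that patient is scored the same way.

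**Conclusion.** The point holds in a limited form. The two CHADS2-based secondary outcomes apply a score without a valve item to every patient over 65, although valve status is known before randomisation, and at score 0 the label reverses with the choice between anticoagulant and antiplatelet. What is established is a mismatch between the fields collected and the outcome rule, not a wrong clinical standard.

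The size is unknown and probably small: about 0.2 to 7 of 361 patients scored not appropriate for this reason, and a swing of at most about 0.9 percentage points in the arm difference, all on the assumed shares above. That valvular patients are eligible is inferred from the absence of any exclusion and from the recording of valve status; no sentence states it. A reader might infer that the main result is at risk. It is not, because the primary outcome counts any reported anticoagulation whatever the score.

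**What to change.** Before unblinded analysis, reconcile the pretest form with the outcome rule:

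- Define both CHADS2-based appropriateness outcomes in patients recorded at pretest as having nonvalvular AF.
- Describe treatment in valvular cases separately by arm, without an appropriateness label.
- Report the all-patient version as a sensitivity analysis.
- State how a missing valve entry is handled. The article mentions an unsure answer for AF type and for thyrotoxicosis, but not for valve status.

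The minimum is to keep the present definition and add the nonvalvular-only analysis as a sensitivity analysis.

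No new data are needed, and because the field precedes randomisation, restricting on it does not introduce post-randomisation selection. The cost is a loss of patients from two secondary outcomes: on the assumed 2% to 15%, 361 × 0.02 = 7 to 361 × 0.15 = 54. It includes patients at higher scores, for whom anticoagulation is not penalised. If valvular cases prove common, the minimum version avoids that loss.
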